## 1.0 ABSTRACT

Sub-Saharan Africa is home to the largest population of adolescents living with HIV (ALWH). Engaging ALWH in HIV care is challenging and reflected in lower rates of viral suppression and higher rates of loss to follow-up as compared to adults in the region. Depression has been identified as a significant barrier to initiating and remaining in HIV care. Indeed, this is the case for ALWH in Malawi where estimates of viral suppression range from 40%-78% and estimates of depression range from 18-26%. Resource-appropriate interventions that improve depression and address engagement in HIV care for ALWH are urgently needed.

The Friendship Bench (FB) is an evidence-based depression counseling intervention delivered by trained, supervised lay health workers. It is proven to reduce depression in the general adult population in low-resource settings but has not been adapted to be youth-friendly or enhanced with peer support to facilitate engagement in HIV care among ALWH. FB is based on problem-solving therapy, which offers an ideal framework for youth-friendly adaption and integration of retention peer support into a proven depression treatment model.

During the formative phase of this project, we conducted qualitative research to better understand how depression impacts HIV care engagement amongst ALWH. We used data gathered in the formative phase to adapt the existing, evidence-based FB protocol to meet the developmental needs of ALWH and to enhance the adapted protocol with peer support to facilitate HIV care engagement among ALWH.

In this second phase, we aim to conduct a 3-arm individual-level randomized pilot trial to determine the feasibility, fidelity, and acceptability of the Adapted and Enhanced FB protocols. The second phase is further working towards our long-term goal of adapting, testing, and scaling up resource-appropriate interventions to reduce depression and improve engagement in HIV care amongst ALWH.

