## 2.0 BACKGROUND, PROBLEM STATEMENT, AND JUSTIFICATION

After conducting formative research on depression and HIV care engagement amongst ALWH, we generated evidence for the adaptation and enhancement of the existing, evidence-based FB protocols. This protocol aims to conduct a 3-arm clinic randomized pilot trial to compare the adapted FB and the enhanced FB to standard of care. This pilot trial is the next step towards reaching our long-term goal of adapting, testing, and scaling up resource-appropriate interventions to reduce depression and improve engagement in HIV care amongst ALWH.

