In this study, we will conduct a 3-arm clinic randomized pilot trial to compare the adapted and the enhanced FB protocols to standard of care. We will determine the feasibility, fidelity, and acceptability of the adapted and enhanced protocols. This pilot trial is the next step towards reaching our long-term goal of adapting, testing, and scaling up resource-appropriate interventions to reduce depression and improve engagement in HIV care amongst ALWH. Information gathered in this proposal will lead to an R01 application for a cluster randomized controlled trial of the adapted and enhanced Friendship Bench interventions to improve depression and engagement in HIV care among ALWH.

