## 6.0 METHODOLOGY

6.1 Design of Study: We will conduct a three-arm individual-level clinical pilot trial across four clinics. Clinics will be randomized either to adapted Friendship Bench (N = 35 ALWH), enhanced friendship bench (N = 35 ALWH), or standard of care (N = 35 ALWH). Participants will all be recruited and followed for 12 months.

The Adapted Friendship Bench (AFB) will be adapted from the existing Friendship Bench intervention protocol to be youth-friendly and address the unique needs of ALWH. Youth friendly adaptation will include selection of young counselors (mixed genders, aged 20-35) who are motivated to work with young people. Counselors will be trained to deliver non-judgmental counseling that respects the privacy and autonomy of ALWH and enables them to make free and informed choices that are relevant to their individual needs. Training will also include discussion of adolescent development and the unique experiences of ALWH related to stigma, disclosure, social relationship issues, and health care access. Counseling sessions will take place in a youth oriented but discrete location within the HIV clinic and be available on weekends to ensure accessibility. AFB will include 6 individual counseling sessions facilitated by counselors attached to one of the study HIV clinics. The first session includes three components called Opening the Mind, Uplifting, and Strengthening, with subsequent sessions building on the first. Opening the Mind refers to the therapeutic process by which, through asking questions, clients are encouraged to open their minds to identify their problems, choose one to work on, identify a feasible solution, and agree on an action plan through an iterative process guided by the counselor. Each structured session lasts 30-45 minutes and will be conducted in a private clinic room in the participant's local language (Chichewa). No specific retention support will be provided, but participants may identify barriers to engagement in HIV care to address during their counseling session. After 4 sessions of individual therapy, the counselor can refer participants not improving or with suicidal ideation to a supervisor trained in mental health to reassess and manage the case. Case management may include additional counseling or pharmacotherapy, at the discretion of the managing clinician.

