**6.2 Place of Study:** The participating health centers will be the Area 18, Area 25, Kawale, and Lighthouse Health Centers. These sites are all government health facilities located in urban Lilongwe, Malawi with ART clinics on their grounds. We selected clinics well matched in terms of staffing levels, services offered, NGO/ancillary program involvement (e.g., all three sites receive training and supervision support from the Lighthouse Trust NGO in Lilongwe), patient volume, and patient population to minimize any important differences between the sites. UNC-Project Malawi will serve as the administrative home for the study and has longstanding relationships with all 4 proposed study sites. UNC Project-Malawi has previously successfully recruited and enrolled adolescents in several sexual and reproductive health studies as well as HIV-related clinical trials.

**6.3 Target Population: ALWH:** We will recruit 105 ALWH from 4 HIV clinics in Lilongwe, Malawi. We aim to recruit for diversity in age, gender identity, and HIV acquisition type. ALWH will be eligible for the study if they are: (1) age 13-19; (2) diagnosed with HIV; (3) scored  $\geq 13$  on the self-reported BDI-II; (4) willing to provide consent (age 18 or 16-17 years old and married (emancipated minors per Malawi law) or assent with parental consent (age 13-17). All HIV+ individuals will be eligible for recruitment including ART initiators, ART re-initiators and established patients. ALWH screening positive for depression who choose not to participate will be referred to a mental health provider.

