#### 6.4 Sampling Techniques and Tools

We will recruit ALWH from 4 HIV clinics in Lilongwe, Malawi and each clinic will be randomized to the adapted Friendship Bench, Enhanced Friendship Bench, or standard of care.

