To assess balance across all 3 study arms at enrollment, we will compare participant characteristics using t-tests for continuous variables and chi-square tests for categorical variables. Quantitative Data: Quantitative measures of feasibility, fidelity, acceptability, and preliminary effectiveness will be summarized using means and standard deviations or proportions and compared across arms using statistical models for continuous or binary outcomes, as appropriate. For feasibility, we will examine the mean number of ALWH enrolled and the proportion of ALWH retained in each of the three study arms (adapted, enhanced, and standard of care). For fidelity, we will examine and compare the proportion of counselors covering at least 80% of checklist items during random direct monitoring sessions across study arms. For acceptability, we will examine and compare the proportion of participants and study staff who found the intervention helpful and easy to deliver across study arms. Changes in depression and engagement in care will be assessed for the 6-month study visit and the 12-month study visit. Generalized estimating equations with an appropriate link for each outcome (i.e., identity link for continuous variables and log link for binary variables) and an exchangeable correlation matrix will be used to examine differences in BDI-II scores, engagement in care, and viral suppression and will account for baseline values of all outcomes and clinic differences. All statistical models will control for any unbalanced confounders. Every effort will be made to minimize missing data, including collecting detailed locator information for the participant as well as for up to two individuals who could help reach the participant should they drop out of contact. However, some missing data is likely to occur. We will examine the data for patterns of missingness and if identified, will conduct sensitivity analyses using inverse probability weights to correct for the bias introduced by the missing data. Qualitative data: Analysis of qualitative exit interview data will involve four steps: 1) reading for content; 2) deductive and inductive coding; 3) data display to identify emerging themes; and 4) interpretation. Codes will be refined during the analysis process and memos will be written for each identified theme.

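### The protocol contradicts itself on whether clinics or individuals are randomized, and under the clinic allocation its methods describe, the promised clinic adjustment of the arm comparison cannot be made

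*Protocol*

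**What the plan says.** **Analysis.** Section 6.7 compares the arms at 6 and 12 months by GEE, in which "an exchangeable correlation matrix will be used to examine differences in BDI-II scores, engagement in care, and viral suppression". The same sentence adds that the models "will account for baseline values of all outcomes and clinic differences". It does not say how clinic enters, or whether the GEE cluster is the participant or the clinic.

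**Allocation by clinic.** Section 6.4: "each clinic will be randomized to the adapted Friendship Bench, Enhanced Friendship Bench, or standard of care". Section 6.1: "Clinics will be randomized either to adapted Friendship Bench (N = 35 ALWH". Section 2.0: "This protocol aims to conduct a 3-arm clinic randomized pilot trial". The end of section 2.2: "we will conduct a 3-arm clinic randomized pilot trial to compare the adapted and the enhanced FB protocols to standard of care".

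**Allocation by individual.** The abstract announces a "3-arm individual-level randomized pilot trial", and the first sentence of 6.1 also uses the individual-level label. No section describes randomizing individuals within a clinic.

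**Numbers.** Section 6.2 names four clinics. Sections 6.1 and 6.5 plan 35 participants per arm and 105 in total.

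**The concern.** Adjusting an arm comparison for clinic needs clinics that contain more than one arm, or enough clinics per arm to measure how much clinics differ. Allocating four clinics to three arms gives neither. The analysis section therefore promises an adjustment that the allocation text does not allow.

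Comparing preliminary effectiveness is the second specific objective (3.2), and section 2.2 says the information gathered will lead to an application for a cluster randomized trial. A between-arm difference described as clinic-adjusted would tell readers that ordinary clinic differences had been removed when they had not.

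**Working it through.** **1. Which unit do the protocol's own figures fit?** Section 6.3 gives 3 counselors per clinic, 6 individual sessions, 35 participants per site and about 70 sessions per counselor.
- A whole clinic of 35 in one Friendship Bench arm: 35 × 6 / 3 = 70. This reproduces the stated load.
- Individuals allocated across four clinics: 70 Friendship Bench participants and 4 × 3 = 12 counselors give 70 × 6 / 12 = 35.

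The stated load fits clinic allocation. It is supporting evidence only: 35 per site over four sites would be 140, not 105, so the site figures are not fully consistent either.

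**2. Can arm and clinic be in the same model?** Take an intercept, 2 arm indicators and 3 clinic indicators, which is 6 columns.
- Clinic allocation: four clinics can fill three arms, with every arm used, in 6 × 6 = 36 ways (6 choices of the pair of clinics sharing an arm, times 3! orderings of the arms). In all 36 the matrix has rank 4. The intercept and clinic indicators already have rank 4, so the arm columns add nothing. None of the three pairwise arm contrasts is estimable.
- Adding the baseline value and a visit term gives 8 columns and rank 6. The shortfall is still 2.
- Individual allocation within the four clinics: rank 6 of 6, and the arm contrasts are estimable with clinic adjusted.

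**3. Does a random or clustered clinic term help?** Between-clinic degrees of freedom within arms are 4 − 3 = 1, all from the one arm that has two clinics. The two-sided 5% t critical value on 1 degree of freedom is 12.7. Such a term can be written down, but it gives no usable separation of arm from clinic.

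**4. What if clinic is left out?** For one clinic of 35 against another, at a single visit and without baseline adjustment, the variance is inflated by 1 + 34 × ICC. The true rate of a nominal 5% test is 2 × (1 − Φ(1.96 / √(1 + 34 × ICC))). The protocol gives no ICC, so the values are assumed:

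| Assumed ICC | Variance inflation | Null rejection rate |
|---|---|---|
| 0.01 | 1.34 | 9% |
| 0.02 | 1.68 | 13% |
| 0.05 | 2.70 | 23% |
| 0.10 | 4.40 | 35% |

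Where one of the two arms has two clinics, the same calculation gives about 8%, 11%, 19% and 30%.

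Section 6.7 also promises baseline adjustment, which removes part of a stable clinic difference. A simulation with the participant as cluster, two follow-up visits, the baseline value in the model, a stable clinic effect and a within-person correlation of about 0.5 gave about 15% at ICC 0.05 and 22% to 27% at ICC 0.10. The inflation is smaller but remains.

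**The case against.** **The trial may be individually randomized.** The abstract and the first sentence of 6.1 say so, and under that reading the adjustment in 6.7 works. This stands, and it makes the point conditional. It does not remove it, because the sentences that state how allocation is done name clinics.

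**Section 6.7 does not specify clinic indicators, and an analysis plan may settle the form.** This stands in part. One clinic-level covariate can be fitted beside the two arm terms (rank 4 of 4), but only the two-clinic arm identifies it. If baseline is modelled as a repeated outcome, an arm-by-time term can be fitted beside clinic indicators (rank 8 of 10, with only the arm main effects lost), but it is confounded with clinic-specific change over time. The failure of estimation is exact only for clinic indicators. The failure to separate arm from clinic is general, and no later choice of model repairs it.

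**The clinics are described as well matched.** Matching may make the clinic variance small, but it cannot supply a within-clinic comparison. Section 6.2 illustrates the matching with "all three sites receive training and supervision support from the Lighthouse Trust NGO", although four clinics are named. A reader might infer that the Lighthouse clinic is the unmatched fourth. The text does not say which three are meant, so that inference is not supported.

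**The consequence could be put more dramatically.** A reader might take clinic as the GEE cluster and conclude that the robust standard errors collapse and nearly every test rejects. The protocol does not name clinic as the cluster. With repeated visits, the participant is the natural one. A reader might also infer that effect sizes will be carried into the next application, but section 2.2 speaks only of information gathered.

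**Effectiveness is secondary.** Section 4 states no hypotheses, and 6.7 acknowledges the small sample. This stands and sets the severity.

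**Conclusion.** The point holds, conditional on the unit of allocation. The protocol contradicts itself on that unit. Under the clinic allocation its methods text describes, the adjustment claimed in 6.7 cannot be delivered. With clinic indicators no arm contrast is estimable, and no other form of clinic term separates arm from clinic.

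The size of the error if clinic is simply omitted depends on ICCs that the protocol does not give. The 9% to 35% range assumes ICCs of 0.01 to 0.10, one clinic of 35 per arm, a single visit and no baseline adjustment, and is somewhat lower at the upper end with baseline included. The rank result needs none of these assumptions.

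A reader might conclude that the adjustment is impossible outright. The documents do not support that, because under individual randomization within clinics it is possible.

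Severity is should-fix. Feasibility, fidelity and acceptability can still be reported by arm, and no sample-size or power figure depends on this model.

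**What to change.** First reconcile the abstract and sections 2.0, 2.2, 6.1 and 6.4 on what is randomized.

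**If clinics are allocated:**
- Delete the reference to clinic differences from 6.7 and state that arm and clinic are confounded.
- Report BDI-II, retention in care and viral suppression descriptively, by clinic and by arm.
- Do not present between-arm differences, p-values or intervals as clinic-adjusted evidence of an intervention effect.

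This costs a few sentences. It does not make the comparison valid; it removes a claim the design cannot support. The price is that secondary effectiveness becomes descriptive, which is consistent with section 4.

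**If individuals are randomized within each clinic:** say so in 6.1 and 6.4, stratify by clinic and keep clinic as a fixed effect in 6.7. If that is already the intention, the cost is wording. If it is not, this changes the allocation itself and must be settled before enrolment, together with the delivery of more than one arm in the same clinic and the site and counselor figures in 6.3.

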## 6.8 Dissemination of Results

We will disseminate our results locally with stakeholders at our clinics in Lilongwe, at UNC-Project Malawi (UNCPM), and through the UNCPM community advisory board. We will also present results at national and international conferences (e.g., IAS, CROI, Academy Health's annual Conference on the Science of Dissemination and Implementation,). Abstracts presented at conferences will also be prepared for publication to disseminate results to the wider scientific community.

## 7.0 ETHICAL CONSIDERATIONS

### 7.1 Human Subjects

Safety considerations. Study staff will evaluate patients for safety who endorse any level of suicidal ideation whether or not they enroll in the study. Safety assessment results will be conveyed to the clinical team as appropriate for further follow-up according to the clinic's standard operating procedures.

### 7.2 Institutional Review Board

Prior to implementation of the pilot trial, all protocol materials will be reviewed by the University of North Carolina Institutional Review Board, in the U.S., and the Malawi National Health Sciences Research Committee (HSRC) before any data collection or analysis occurs. The study will also be reviewed and informed by the existing community advisory board (CAB) of UNC Project in Malawi. The CAB will review the study protocol prior to implementation and provide feedback. The CAB meets monthly. All research procedures will adhere to Malawian and US ethical standards for research involving human subjects.

### 7.3 Confidentiality, Risks, and Risk Minimization

Risks of loss of confidentiality or social harms to participants will be minimized by 1) training of study staff in the ethical conduct of research; 2) strict protection of confidentiality and personal information; 3) close monitoring of social harms with appropriate IRB reporting.

Discussing personal information – Study participation will include discussion of sensitive topics with ALWH during counseling sessions and peer support sessions. All study counselors will be trained to keep all

information confidential. Research assistants will be trained, and participants informed, that they can pause or discontinue a research interview at any time if they find the topic upsetting.

Data security - All study data, including interview guides, audio recordings of interviews, interview transcribes, and logbooks will be kept in a locked cabinet at the UNC Project data center, where they will be maintained in a locked office at UNC Project accessible only to the principal investigator. Interviews that are transcribed and computerized will be stored on the secure central server at UNC Project. For analysis purposes, data will be de-identified before coding and analysis. Only the principal investigator, data entry personnel, and assigned data analysts will have access to the de-identified electronic study database.

Preventing Discomfort: The surveys, counseling sessions, and peer support activities may cause discomfort for some participants. Efforts will be made to minimize this discomfort by assuring that participants are informed beforehand about the nature of the interaction and that the interaction is completed in a private setting. Participants will be informed that they have the right to decline participation in the study, to refuse to answer any questions, or to withdraw at any time. The consent form will also emphasize that personal information (and inclusion in the study based on HIV and depression status) will be shared during focus groups and confidentially cannot be assured.

Addressing Harms. Our overall goal is to protect the well-being of ALWH, thus if sexual or physical abuse is reported, we will ensure ALWH are referred to a local organization that deals with sexual abuse/violence so that the individual receives appropriate care or to a local social worker. If a study team member comes to believe that a participant is experiencing a crisis (which the participant may or may not recognize) they also may refer to local social workers for counseling or psychosocial support. Examples would include a participant who is having an extreme emotional reaction when discussing the challenges of living with HIV, or a participant whose behavior suggests possible undiagnosed mental illness. These revelations of harm are not common but may occur on a limited basis, necessitating that study protocols be in place to respond appropriately.

At each clinic from which we will recruit participants, we will identify a provider to act as the “clinic lead” for navigation services. This person is a chief point of contact for the study team. When a situation arises where study staff learns of a potential risk of harm to a participant, the following steps will be followed:

- (1) The study team member learning of the problem will immediately inform the PI.
- (2) If the participant is actively in distress and at the clinic, the study team member will refer the participant to the clinic lead (or, if the lead is not available, to another clinic provider) for immediate evaluation.
- (3) If the participant is actively in distress and not at the health center, the study team member will offer to meet the participant and accompanying them to the health facility for immediate referral.
- (4) If the participant is not actively in distress, then the study investigators, project manager, and other appropriate project supervisory staff will develop a plan for referring the participant to the clinic lead. As appropriate, the project team may consult the clinic lead in developing the plan. (All consent forms will note that investigators may need to break confidentiality when there is a threat of harm to self or others.) The timing and most appropriate means of effecting a referral will be dependent on the nature of the problem. For example, if a participant reports child abuse in the home, then it would be necessary to involve appropriate social services to investigate the problem. By contrast, if a participant reports that she/he is facing ongoing (but not life threatening) emotional abuse from a partner, then it may make more sense for the navigator to first approach the participant and encourage her/him to meet with a clinic provider or with other social support services in the area.
- (5) Study investigators will inform all governing IRBs of the incident and update the IRBs as necessary on the outcomes of efforts to intercede and resolve the harm.

